## Abstract

**Background::**

As one of the important manifestations of neurogenic bowel dysfunction, constipation is characterized by high incidence and harmful effects. It has a negative impact on both physical and psychological health of patients. And there are no effective treatment options for this type of disease clinically. Therefore, this study is designed to examine the effect of the therapy of “combination 3 methods progression” in patients with neurogenic bowel dysfunction (constipated type).

**Methods::**

This is a randomized, controlled, parallel-design clinical trial. A total of 60 patients with neurogenic bowel dysfunction (constipated type) will be randomly assigned to intervention group and control group. The control group will receive 4 weeks of usual rehabilitation care, the intervention group will receive 4 weeks of the therapy of “combination 3 methods progression” in addition to usual rehabilitation care. The primary outcome is the number of spontaneous bowel movement per week. Secondary outcomes are stool characteristics, degree of difficulty in defecation, level of anxiety, level of depression, and level of self-efficacy.

**Discussion::**

The interventions of this protocol have been programmed to alleviate constipation in patients with neurogenic bowel dysfunction. Findings may provide preliminary evidence for clinical efficacy of the therapy of “combination 3 methods progression.”

**Trial registration::**

Chinese Clinical Trial Registry, IDF: ChiCTR2000041463. Registered on December 26, 2020.

## Introduction

1

### Background

1.1

Neurogenic bowel dysfunction (NBD) is a disorder of bowel dysfunction caused by neurological deficits (including nerve damage, neurological disease, and congenital defects in the nervous system).^[1,2]^ The main clinical manifestations are constipation, fecal incontinence, abdominal pain, and distention.^[3–5]^ Spinal cord injury (SCI) and stroke are among the common primary diseases of NBD.^[6]^ According to the epidemiological data, about 56% to 95% of SCI patients have constipation,^[3,7]^ with 30% of them being severely constipated.^[8]^ And the prevalence of constipation in stroke patients varies from 30% to 66%.^[9–11]^ The pathogenesis of NBD is complex and varies with the location and severity of neuropathy,^[12]^ but it is very certain that it not only causes harm to physical and psychological health, but also causes patients to receive serious effects on daily life and social relationships.^[13–15]^ Therefore, bowel management is very necessary for NBD patients.

Currently, treatments for NBD vary and mainly include dietary management,^[1,16]^ medication (e.g., laxatives, suppositories),^[17,18]^ frequency electric stimulation,^[19]^ finger stimulation,^[20,21]^ and transanal irrigation.^[22]^ In addition, traditional Chinese medicine (TCM) therapies, such as acupuncture and moxibustion,^[23]^ electroacupuncture,^[24,25]^ and scrapping therapy,^[26]^ and so on, are also slightly effective in the treatment of NBD. Unfortunately, many of them are time-consuming and costly, with poor compliance and limited effectiveness. Thus, there is a need for a safer, more convenient, and effective therapy to manage the bowel.

The therapy of “combination 3 methods progression” is a rehabilitation program that combines tradition Chinese medicine and Western medicine. It includes 3 aspects: pestle needle therapy, Tuina, and functional exercise. Pestle needle therapy was developed in the 1970s by Zhong-Yu Li, a famous professor in Chengdu University of TCM.^[27]^ It is an important branch of acupuncture in tradition Chinese medicine. It stimulates the acupoints on the body surface through certain techniques. The needles do not pierce the skin, but only act on the internal organs and meridians, thus achieving the effect of treating diseases and strengthening body.^[28,29]^ It has the advantages of precise acupoints, painless, noninvasive, easy to operate, and widely applicable to the population.^[30,31]^ Pestle needle has the dual effect of acupuncture and massage,^[32,33]^ and has been widely used in the treatment of various diseases.^[34]^ Tuina is a traditional form of manipulative therapy, and is essentially a Chinese medical massage.^[35,36]^ The therapeutic effect is achieved by applying a certain force to the muscles or soft tissues of the body through the operator's fingers, hands, elbows, knees, and feet.^[37]^ Tuina has been shown to have a positive impact in the treatment of constipation.^[38]^ Functional exercise is a common form of rehabilitation therapy in Western medicine. A few studies have shown that functional exercise can improve the physical and mental health of people with constipation, and its safety has been proven.^[39–41]^ In our previous studies, we also found that constipation symptom in NBD patients was reduced by instructing them to perform functional exercises, but it needs further confirmation. The therapy of “combination 3 methods progression” was developed by professor [name] on the basis of long-term clinical practice and experience in disease rehabilitation. It emphasizes the combination of TCM and modern rehabilitation techniques. In past clinical studies, this therapy has been shown to be effective in chronic diseases.^[42]^ At present, there are no clinical studies on the application of it to NBD patients. Based on these uncertainties, the aim of our study is to determine whether “combination 3 methods progression” is effective in patients with NBD.

### Objectives

1.2

In this study, the first objective is to investigate the clinical efficacy of “combination 3 methods progression” in the treatment of constipation in NBD patients. The second objective is to determine whether the therapy can reduce anxiety and depression in NBD patients. The third objective is to explore a more scientific approach to bowel management for NBD patients.

### Trial design

1.3

This is a randomized, controlled, parallel-design clinical trial which will be implemented from March 2021 to March 2022. The study follows the Declaration of Helsinki Principles.^[43]^ It was allowed by Medical Ethics Committee of Affiliated Hospital of Chengdu University of TCM (2020KL-076), and has been registered on the Chinese Clinical Trial Registry (Registration No. ChiCTR2000041463). The protocol will be reported according to Standard Protocol Items: Recommendations for Interventional Trials statement. The flowchart of the trial is shown in Figure 1.

**Figure 1 F1:**
[figure not shown]
Trial flow chart.

## Methods

2

### Study setting, recruitment, and informed consent

2.1

The trial will be carried out at the Affiliated Hospital of Chengdu University of TCM. Sixty patients will be recruited by posting recruitment ads on hospital outpatient clinics and hospital ward bulletin boards. A contact number will be included in the recruitment information so that potential participants can contact us. The study will be available to all NBD patients (constipated type) interested in the therapy of “combination 3 methods progression.” Two trained investigators will describe the study to the patients (if applicable), including the purpose, content, duration, and frequency of interventions, benefits, possible discomfort and risks, and associated costs. All patients who agree to participate in this study will sign an informed consent form.

### Inclusion criteria

2.2

(1)Meet the international standard for neurological classification of SCI developed by American Spinal Injury Association: Grades B to D, confirmed by computed tomography (CT) or magnetic resonance imaging (MRI)^[44]^; or meet the diagnostic criteria for cerebral hemorrhage,^[45]^ confirmed by CT or MRI; or meet the diagnostic criteria for cerebral infarction,^[46]^ confirmed by CT or MRI;(2)Meet the Roman IV diagnostic criteria for functional constipation^[47]^;(3)With symptoms of anxiety and depression;(4)Aged 20 to 80 years;(5)With stable vital signs, clear consciousness, normal communication, and expression skills;(6)Sign an informed consent form and submit to the arrangements of the subject group.

Note: Only patients who meet the above 6 criteria can be included in this study.

### Exclusion criteria

2.3

(1)With serious primary diseases of the heart, liver, kidney, and endocrine system;(2)Pregnant and lactating patients;(3)With severe clotting disorders;(4)With psychiatric disorders;(5)Skin allergies or breakouts in the treated area;(6)Already participated in other trials.

Note: Patients who meet any of the above criteria should be excluded in this study.

### Randomization and blinding

2.4

Randomization will be based on a randomization sequence generated by the software SPSS25.0. Patients will be randomized at a 1:1 ratio into intervention group and control group. Randomization will be performed by a statistician who is not involved in this study. Data managers, and outcome assessors will be unaware of the outcome. However, due to the trail's nature, the doctors, nurses, and therapists will not be blinded.

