### Data management and confidentiality

2.7

All patients will be numbered according to the order of admission time and randomly grouped. To avoid the occurrence of measurement bias, relevant data were collected by uniformly trained individuals who were not involved in the intervention process and were not aware of the groups. All data obtained from NBD patients will be recorded on case record form and entered into the software SPSS25.0. Two different individuals will enter data to ensure the accuracy. The obtained data, including checklists, scales, questionnaires, and informed consent forms will be stored in locked file cabinets, and will be kept strictly confidential. Only researchers will have access to the participants’ data in the study.

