### Sample size

2.8

In this study, the following formula was selected to estimate the sample size:$$n=\frac{2{\left(\mu_{\alpha }+\mu_{\beta }\right)}^{2}P(1-P)}{\delta^{2}},P=(P_{1}+P_{2})/2$$

*P*_1_ is the effective rate of intervention group, *P*_2_ is the effective rate of control group. Based on pre-experimental results, *P*_1_ = 85%, *P*_2_ = 50%. According to statistical requirements, the *α* was set to 5%, and the *β* was set to 80%. By looking up the table of random numbers, we get $\mu_{\alpha }$ at 1.96, $\mu_{\beta }$ at 0.84, the estimated sample size was 28 patients per arm. To ensure the replenishment of lost samples, the sample content is increased by 20%, so the final sample size was 30 patients per arm.

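### Spinal cord injury and stroke patients are pooled in a 60-patient trial, with no stratification by cause and no adjustment for it stated

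*Protocol article*

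**What the plan says.** Section 2.2 (Inclusion criteria) admits three diagnoses: SCI of American Spinal Injury Association grades B to D, "or meet the diagnostic criteria for cerebral hemorrhage", or the criteria for cerebral infarction. It sets no quota and gives no expected mix.

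Section 1.1 (Background) treats the site of the lesion as relevant: "The pathogenesis of NBD is complex and varies with the location and severity of neuropathy". It puts the prevalence of constipation at 56% to 95% in SCI and 30% to 66% in stroke.

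On allocation, section 2.4 (Randomization and blinding) says "Randomization will be based on a randomization sequence generated by the software SPSS25.0" and "Patients will be randomized at a 1:1 ratio into intervention group and control group". A statistician outside the study performs it. Section 2.7 (Data management and confidentiality) adds how patients enter the sequence: "All patients will be numbered according to the order of admission time and randomly grouped". No section mentions strata, blocks or minimisation.

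Section 2.8 (Sample size) ends at 30 patients per arm. Section 2.9 (Statistical analysis) names paired or independent t-tests for continuous variables and Pearson's chi-squared test for categorical ones. It names no covariate.

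**The concern.** The primary outcome is the weekly number of spontaneous bowel movements. The article itself says that the mechanism of bowel dysfunction depends on where the nervous system is damaged, so cause (SCI or stroke) is a plausible prognostic factor. It is also known for every patient before randomisation, because it is part of eligibility.

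The text as published neither balances cause by design nor removes its influence in the analysis. In a 60-patient trial the arms can then differ visibly in case mix. Suppose the mean outcome differs by D between SCI and stroke patients. A 20-point gap in SCI share then shifts the observed difference between arms by 0.20 × D in that particular trial. Variation in outcome due to cause also stays in the residual error and widens the confidence interval. The stake is precision and readability of the result, not validity of the test.

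**Working it through.** **1. The plan's own sample size.** Inputs from section 2.8: effective rates 0.85 and 0.50, so P = (0.85 + 0.50)/2 = 0.675 and δ = 0.35; normal quantiles 1.96 and 0.84.

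n = 2 × (1.96 + 0.84)² × 0.675 × 0.325 / 0.35² = 28.08 per arm.

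The stated 28 reproduces (29 if rounded up). The step to 30 is an increase of 30/28 − 1 = 7%, not the stated 20%. That is a separate matter and plays no part below.

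**2. Chance of a gap in cause, arms fixed at 30/30.** Inputs: 60 patients (abstract, section 2.1) and 30 per arm (section 2.8). The number K of SCI patients is an assumption, taken as 12 to 30 (20% to 50%). Without stratification, the SCI count X in one arm is hypergeometric:

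P(X = x) = C(K, x) × C(60 − K, 30 − x) / C(60, 30).

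The SCI shares differ by |2X − K|/30. A gap of 20 points or more means |2X − K| ≥ 6.

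| SCI patients K | Share of 60 | Smallest split that counts | Probability |
|---|---|---|---|
| 12 | 20% | 9 vs 3 | 10.4% |
| 15 | 25% | 11 vs 4 | 7.2% |
| 20 | 33% | 13 vs 7 | 17.0% |
| 24 | 40% | 15 vs 9 | 18.7% |
| 30 | 50% | 18 vs 12 | 19.6% |

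The figures do not rise steadily because the counts are whole numbers: with K = 15 the first qualifying gap is 7/30 = 23 points. The range is about 7% to 20%. Under simple randomisation, where arm sizes also vary, the same event has a probability of about 6% to 16%. The finding therefore does not depend on which kind of unstratified list is used.

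**3. What stratification would do.** As an illustration, take blocks of 4 (size assumed) within two strata. The arms differ by at most 2 within each stratum. With K = 30, the worst opposite imbalances give SCI 16 vs 14 and stroke 14 vs 16. That is a gap in SCI share of 16/30 − 14/30 = 6.7 points. The arms differ by at most 4 overall, a split of 28/32.

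**4. Do unequal arms matter?** Power on the article's rates, two-sided 5%, is Φ[(0.35 − 1.96 × SE₀)/SE₁], with SE₀ the pooled and SE₁ the unpooled standard error. At 30/30, SE₀ = √(0.675 × 0.325 × 2/30) = 0.121 and SE₁ = √((0.85 × 0.15 + 0.50 × 0.50)/30) = 0.112, which gives 84.3%. At 25/35 it is 82.8% to 83.9%, depending on which arm is smaller. At 28/32 it is about 84%. Simple randomisation of 60 gives exactly 30/30 in 10.3% of lists and 25/35 or worse in 24.5%, but the loss of power is small.

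**The case against.** The strongest reply is that this rests on silence. The article never calls the list unstratified, it refers to a full protocol, and block or stratum details and covariate adjustment are often left to such a document or to an analysis plan. This stands in part: an unstratified list is an inference. But section 2.7 does describe one numbering of all patients by admission, which points away from separate lists by cause, and section 2.9 does name its tests.

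A second reply is that the prevalence figures in section 1.1 do not show that cause predicts outcome here. They concern all SCI and all stroke patients, their ranges overlap, and every enrolled patient must already meet the Rome IV constipation criteria. This is right. The article gives no size for the effect of cause, so the benefit of stratifying is conditional on cause being prognostic.

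A reader might also draw three stronger conclusions, none of which the article supports:

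- **That 30 per arm is not secured.** This holds only under simple randomisation, which is not stated. A random permutation of 30 and 30 fits the article equally well, and even 25/35 leaves power at about 83%.
- **That imbalance in cause is likely.** A gap of 20 points or more is absent in at least about 80% of lists.
- **That cause would be confounded with treatment so that the t-test is invalid.** Chance imbalance under random allocation does not bias the estimate or invalidate the test.

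**Conclusion.** The point holds as a recommended improvement, not as an error that invalidates the trial. The plan as published pools SCI and stroke, states no balancing on cause and names no adjustment for it, although its own background says that the mechanism varies with the lesion.

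The size is a probability of about 7% to 20% that the arms differ by at least 20 percentage points in SCI share. This rests on three assumptions: the list is unstratified, the arms are 30/30, and SCI patients make up 20% to 50% of the 60. The consequence is lost precision and a harder reading of the result, to the extent that cause is prognostic, which the article does not quantify. No claim about arm sizes is needed.

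**What to change.** - In section 2.4, have the independent statistician prepare a permuted-block list with varying block sizes, 1:1 within two strata (SCI; stroke, meaning haemorrhage or infarction), and state this.
- In section 2.9, replace the unadjusted t-test for the primary outcome with a linear model (ANCOVA) that includes cause (SCI vs stroke) as a covariate.
- If enrolment has begun, leave the list alone and prespecify the covariate only, before data are unblinded. The adjusted analysis still recovers most of the benefit.
- If the full protocol already stratifies by cause, say so in section 2.4 and carry the stratum into the analysis.

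The cost is one regenerated list and one degree of freedom. The change of primary analysis from a t-test to a model must be written down. No extra patients, visits or staff are needed, because cause is already recorded at eligibility.

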### Interventions

2.5

#### Intervention description

2.5.1

##### Control group

2.5.1.1

Receiving usual rehabilitation care, the duration is 4 weeks.

(1)Dietary care: nurses will instruct patients to eat more fruits, vegetables, coarse grains, and other high-fibre and nutrient-rich foods, avoid beans and milk, and ensure adequate daily intake of water to soften the stools, thus providing a smooth bowel movement.(2)Defecation care: use suppositories or laxatives as an aid to defecation as prescribed by the doctor. If the patient is severely constipated, perform a manual cleansing enema for defecation.(3)Psychological care: ① Nurses will communicate with patients in a cordial and amiable manner in order to establish a good nurse-patient relationship. ② Actively explain to patients about constipation to increase their knowledge of this disease. ③ Take the initiative to communicate with the patients’ family to increase social support and patients’ confidence. ④ Encourage patients to divert negative emotions by listening to music and chatting, and so on.

##### Intervention group

2.5.1.2

Receiving the therapy of “combination 3 methods progression” in addition to usual rehabilitation care.

###### Pestle needle treatment

2.5.1.2.1

The tool used in this treatment is Taiji pestle needle, which was designed by Li's pestle needle heritage workshop of Affiliated Hospital of Chengdu University of TCM. It includes 4 different types of needles: Seven luminaries-mixed Yuan Pestle, Five Star-Three Terrace Pestle, Vajra Pestle, and Kui Xing Pen (Fig. 2). They are all in full brass and their lengths are 10.5 cm, 11.5 cm, 10.5 cm, and 8 cm respectively. The method of holding pestle needle includes pencil operated method (Fig. 3) and straight grip method (Fig. 4). Pencil operated method is suitable for the treatment of head, face, chest, abdomen, and areas with few muscles of extremities. Straight grip method is suitable for the treatment of waist, back, sacrum, and areas with rich muscles of extremities. Treatment techniques include Diankou, Shengjiang, Kaihe, Yunzhuan, and Fenli (Table 1). The criteria for the selection of acupoints refer to the book “Pestle Needle Studies” published by the Chinese Press of Traditional Chinese Medicine.^[48]^ There are 2 specific acupoints: Bazheng acupoints (8 array acupoints) and Heche Road (the road for the vehicle). Using an acupoint as Zhong Gong, a circle is drawn with a certain distance (usually is 3 cun, and 1 cun≈20 mm) as a radius from the center of Zhong Gong. This circle is then divided into 8 equal parts (heaven, earth, wind, cloud, dragon, tiger, bird, and snake) to form 8 acupoints, and is called the outer 8 array. The distance from Zhong Gong to the outer 8 array is then divided into 3 equal parts and 2 circles are drawn, which are called the middle and inner 8 array. The acupoints on the inner, middle, and outer 8 array form the Bazheng acupoints (Fig. 5). The back of the human body has 7 Heche Road (Fig. 6), one of which is the posterior median line and the other 6 are parallel lines of 0.5 cun, 1.5 cun, and 3 cun apart from the posterior median line. The number of acupoints selected for this therapy is 13 (Table 2). The operation steps are as follows: ① Take the 8 array acupoints of Shendao (DU11), use Vajra Pestle and Seven Luminaries-Mixed Yuan Pestle to perform Fenli technique for about 3 minutes, then use the tip of Five Star-Three Terrace Pestle to perform Diankou technique for about 3 minutes. ② Take the 8 array acupoints of Yaoyangguan (DU3) and perform with the same tools and techniques as above. ③Take the Heche Road of Da zhui (DU14) to Changqiang (DU1), use the tip of the Seven Luminaries-Mixed Yuan Pestle to perform Shengjiang technique for about 5 minutes or until skin is slightly red. Then use the tip of Kui Xing Pen to perform Kaihe technique and the tip of Five Star-Three Terrace Pestle to perform Diankou technique for about 3 minutes respectively. Finally, use the shank of Vajra Pestle to perform Yunzhuan technique for about 1 minute. ④ For those who suffer from emotional discomfort and sadness, add Zhangmen (LR13), Sanyinjiao (SP6), and Taichong (LR3). For those who have weak bowel movements, add Tianshu (ST25), Zushanli (ST36), and Shangjuxu (ST37). For those who like to eat hot and spicy food, and drink insufficient water, add Xuehai (SP10), Weizhong (BL40), Chengshan (B57), Zushanli (ST36), Sanyinjiao (SP6), and Baliao acupoint. The frequency of treatment is about once a day, 5 days a week and the duration is 4 weeks.

**Figure 2 F2:**
[figure not shown]
Diagram of pestle needle (from left to right: Kui Xing Pen, Vajra Pestle, Five star-Three terrace pestle, Seven Luminaries-mixed Yuan Pestle).

**Figure 3 F3:**
[figure not shown]
Pencil operated method.

**Figure 4 F4:**
[figure not shown]
Straight grip method.

**Table 1 T1:** The detailed methods of treatment techniques for pestle needle therapy.

Treatment techniques	Detailed methods
Diankou	The tip of pestle needle is tapped repeatedly on the acupoints, like a sparrow pecking. It is suitable for acupoints with small areas.
Shengjiang	Use the tip of pestle needle to touch the skin at acupoints, then move up and down along the longitudinal axis of body, move up is named “sheng” and move down is named “jiang.” It is suitable for acupoints with large areas.
Kaihe	Use the tip of pestle needle to touch the skin at acupoints, and apply force in a vertical direction, as much as the patients can tolerate, it is named “kai.” Then stop applying force and lift pestle needle slowly upwards, without the tip leaving the skin of acupoints, it is named “he.” It is suitable for acupoints with small areas.
Yunzhuan	Use the tip of Seven luminaries-mixed Yuan Pestle and Five star-Three Terrace Pestle, or use the shank of Vajra Pestle and Kui Xing Pen firmly against the skin at acupoints, and move it in a clockwise or counterclockwise direction.
Fenli	Use the tip or the shank of pestle needle to touch the skin at acupoints, move from side to side along the horizontal axis of the body, it is named “fen.” Then move up and down along the longitudinal axis of the body, it is named “li.” It is suitable for acupoints with large areas.

